#### B3. DESCRIPTION OF RESEARCH PROTOCOL

##### Study Design – Overview, Methods, Procedures

| We propose a two-arm prospective randomized clinical trial with non-randomized third group to evaluate the effect of Tai Chi on age-related loss of complexity.    **Arms 1 and 2**  will consist of a total of 60 Tai Chi–naïve healthy older adults (aged 50-79) will be randomized to either six months of Tai Chi training, or to a waitlist control receiving standard medical care. Our primary outcomes are complexity-based measures of cardiovascular (heart rate, HR), balance (center of pressure, COP) and locomotor (stride interval) dynamics assessed at 3 and 6 months. Secondary outcomes include measures of physical and psychological function and tests of physiological adaptability also assessed at 3 and 6 months. A secondary goal of this study is to characterize the relationship between complexity biomarkers, measures of function, and adaptability. This pilot study will inform a future more definitive trial by providing information on recruitment and retention, compliance, dose-dependent effects, preliminary estimates of effect size, and the optimal biomarkers of complexity, function, and adaptive capacity. Figure 1 summarizes the overall study design.  **Arm 3** (Tai Chi Expert Group): A total of 30 healthy older adults (aged 50-79) each with over 5 years of Tai Chi practice will comprise the third group of this study. In a single visit, primary outcomes related to complexity-based measures of cardiovascular (heart rate, HR), balance (center of pressure, COP) and locomotor (stride interval) dynamics), as well as secondary outcomes related to physical and psychological function and tests of physiological adaptability will be assessed. This group of Tai Chi experts will serve as a ‘gold standard’ of what the long-term physiological impacts of tai chi training might provide, and thus serve as an informative reference population to our current Tai Chi Naïve and Tai Chi Novice (i.e. after 6 months training) groups.  **Arm 4** (Young Comparison Group): A total of 15 healthy young adults (aged 25-35) with no prior Tai Chi experience will comprise the fourth group of this study. In a single visit, primary outcomes related to complexity-based measures of balance (center of pressure, COP) and locomotor (stride interval) dynamics, as well as secondary outcomes related to physical function and physiological adaptability will be assessed. This group of healthy young adults will serve as a reference comparison group for balance and gait measures before any age-related decline begins.  **Tai Chi intervention**  All Tai Chi instruction will take place at one of the Tai Chi schools within our research network, which was established and used in a prior NIH funded Tai Chi trial of ostepenic women (BIDMC protocol # 2007P––000162). These schools were chosen to meet specific criteria ensuring they provide valid, stable Tai Chi programs led by experienced teachers. Importantly, since participants are being asked to make a six month commitment to Tai Chi training, allowing them to receive training at a school they choose within their community will increase the likelihood of protocol adherence. Administering the intervention through community Tai Chi schools also affords a high level of ecological validity, as participants will be exposed to a number of traditional components of Tai Chi training that are often absent in fixed protocols provided in medical settings.^77,152^ Finally, because of the inclusion of multiple Tai Chi instructors and well-defined but slightly varying protocols, the results of this study will have good generalizability—applying not only to a single protocol of Tai Chi taught by one teacher, but to a range of approaches that share a common, well-defined set of criteria.  Participants randomized to Tai Chi will be required to attend, on average, two classes per week over the six months of the intervention. They will also be asked to practice a minimum of 30 minutes, two additional days per week. The majority of schools in our network provide DVD’s or printed materials to facilitate home practice. Compliance with this training schedule will be monitored using a combination of class attendance cards that are signed by Tai Chi instructors following each visit, and participant-completed home practice logs employing protocols developed in our current Tai Chi for osteopenia study. Participants will be asked to send class attendance and home practice logs to study staff monthly using prepaid envelopes provided at the beginning of the study. If attendance and/or practice logs are not submitted on time, the study coordinator will call the participant within 7 days of the due date. Effort will be made to keep subjects actively engaged in the protocol. If a participant is non-compliant, the study coordinator will contact the participant and work with them to overcome any barriers to participation.  **Measurement protocols**  Overview of measurement protocol  All three arms of the study will complete our baseline measurement protocol including acquisition of 1) steady-state dynamics of the cardiovascular, locomotor and balance control systems, 2) measures of the ability of these systems to respond to imposed stressors, and 3) more traditional measures of function and Health Related Quality of Life (HRQOL). Additionally, traditional linear outcome measures for heart rate variability, gait, and balance will be assessed for comparison with complexity measures. All measurements will be assessed at baseline. Only Arms 1 and 2 (Tai Chi Novices and Control Group) will repeat all measures at 3 and 6-months. All outcome assessors will remain blinded with respect to treatment allocation. Table 1 provides a summary of these measures, as well as additional screening tools.  **Table 1. Summary of outcomes and measures and associated variables (see below)**   \| **Temporal dynamics during steady-state conditions** \| **Physiological measure** \| **Testing methods** \| **Outcome variable** \| \| --- \| --- \| --- \| --- \| \|  \| Heart rate (HR)º \| Beat-to-beat variation measured using ECG for a 30 minute during seated quiet resting \| HR complexity \| \|  \| Standing balance \| Center of pressure (COP) dynamics during quiet standing with eyes open \| COP complexity \| \|  \| Gait \| Stride–to-stride interval at preferred speed during a 20 minute period \| Stride complexity \| \| **Adaptive capacity** \| Heart rateº \| Sit to stand test \| Max change in heart rate \| \|  \| Standing balance \| Eyes closed  Cognitive dual task \| Change in COP complexity  Change in magnitude of COP  displacement \| \|  \| Gait \| Cognitive dual task \| Change in average stride  variability \| \| **Function and HRQOL** \| Exercise capacity \| Max walking speed \| m/sec \| \|  \| Musculoskeletal strength/power \| a. Lower extremity power (Jump test)  b. Grip strength (dynamometer) \| a. Maximum height of  jump (cm)  b. kg \| \|  \| Timed Up and Go (TUG) \| Standardized test of time to rise from chair, walk 10 feet to and from cone, return to seated position \| Functional status \| \|  \| Functional reach \| Subject reaches forward with hand and arm  extended and parallel to a yardstick at  shoulder height to reach as far as possible without taking a step \| Functional Status \| \|  \| Clinical balanceº \| Single leg balance with eyes open and closed \| Maximum time on balance \| \|  \| Range of motionº \| a. Goniometry of lower extremity (hips, knees, ankles bilaterally)  b. Sit and reach test (back and leg flexibility) \| a. Degrees of motion  b. cm \| \|  \| Respiration rateº \| Nasal thermoster attached to volume gas monitor \| Breathing frequency \| \|  \| Electrical potential \| Skin surface electrical potential \| Skin surface electrical potential at select segments along arms and legs \| \|  \| Moodº \| Profile of Mood States \| Indices of 6 domains of mood \| \|  \| Cognitive functionº \| Trail Making Test A and B  Controlled Oral Word Association Test  Backwards Digit Span Test \| Time to complete test (sec)  Number of words recalled/min  Number of digit sequences  correctly repeated \| \|  \| HRQOLº \| SF-36 \| Indices of physical and  mental health in 8 domains \| \|  \| Physical activityº \| Physical Activity Status Scale  Arm 3 ONLY: Frequency of Tai Chi and related exercise training \| Index of physical activity  during prior week \| \| **Protocol adherence, screening, and potential confounders** \| Tai Chi training*º \| Teacher reported class attendance records  Self-reported home practice logs \| Numbers of classes/month  Hours of home practice/month \| \|  \| Cognitive function \| Mini-mental state exam \| Index reflecting 5 domains of  cognitive health \| \|  \| Expectancy regarding intervention*º \| Expectancy/credibility questionnaire \| Numerical scale (1-5) \| \|  \| Satisfaction regarding intervention*º \| Satisfaction questionnaire \| Numerical scale (1-5) \| \|  \| Exit Interview*º \| Qualitative exit questions concerning study experience. \| Six open-ended questions \|   (Key provided on following page)  * Arm 3 (The Tai Chi Expert Group) will not be subjected to these measures.  º Arm 4 (Young Comparison Group) will not be subjected to these measures.  Flow of participant through protocol measurements (Arm 1,2, and 3)  All testing will take place in the Syncope and Falls in the Elderly (SAFE) laboratory, located within the CRC at BIDMC. Subjects will be asked to arrive at the laboratory between 8:00 -10:00 a.m. We expect testing to occur for approximately 4 hours. Participants will first meet with a CRC study nurse who will confirm eligibility questions asked during the phone screen. A study investigator will then ask participants to review and sign the informed consent form. The CRC study nurse will then review participant’s health history, obtain vital signs, ECG, height and weight. Study personnel will implement the mini-mental state exam. Participants that meet all eligibility criteria will then undergo standard study related measurements that will be conducted by [name] and/or a TBD research assistant, with oversight by [name], the SAFE laboratory director.  The sequence of testing we will employ is based on protocols regularly conducted in the SAFE laboratory,^140,153^ and has been designed to minimize fatigue and patient burden, and maximize the quality/validity of the data collected. Each stage of testing, as well as repeated assessments of specific tests, will be separated by an appropriate resting period. The total time for completion of measurements is estimated to be 4 hours. The general order of procedures is as follows:  a. Fitting of HR instrumentation, measurement of resting HR dynamics, sit-to-stand test, and timed up and go test  b. Steady state and challenged center of pressure (balance) testing  c. Preferred speed stride dynamics and dual task walking  d. Break with snack  e. Completions of cognitive, mood, HRQOL, and exercise behavior instruments  f. Physical function tests (maximum walking speed, balance, jumping height, grip strength, range of motion)  Flow of participant through protocol measurements (Arm 4 – Young Comparison Group)  All testing will take place in the Syncope and Falls in the Elderly (SAFE) laboratory, located within the CRC at BIDMC. We expect testing to occur for approximately 2 hours. Participants will first meet with a CRC study nurse who will confirm eligibility questions asked during the phone screen. A study investigator will then ask participants to review and sign the informed consent form. The CRC study nurse will then review participant’s health history, obtain vital signs, height and weight. Study personnel will implement the mini-mental state exam. Participants that meet all eligibility criteria will then undergo standard study related measurements that will be conducted by [name] and/or a TBD research assistant, with oversight by [name], the SAFE laboratory director.  The sequence of testing we will employ is based on protocols regularly conducted in the SAFE laboratory,^140,153^ and has been designed to minimize fatigue and patient burden, and maximize the quality/validity of the data collected. Each stage of testing, as well as repeated assessments of specific tests will be separated by an appropriate resting period. The total time for completion of measurements is estimated to be 2 hours. The general order of procedures is as follows:  a. Timed up and go test  b. Steady state and challenged center of pressure (balance) testing  c. Preferred speed stride dynamics and dual task walking  d. Physical function tests (maximum walking speed, balance, jumping height, grip strength, range of motion)  Details of measurement procedures  *Cardiovascular measures:* Steady-state HR dynamics will be assessed during seated rest with spontaneous breathing. To collect the sufficient number of heartbeat cycles for complexity measures, HR will be assessed for 30 minutes. Additionally, two 5-minute periods of HR dynamics will also be assessed during paced breathing (15 and 6 breaths per minute); paced breathing will enable the assessment of cardiovascular dynamics and linear measures of HR variability while controlling for the potentially confounding effects of respiration.^154^ During each breathing pattern, HR and respiration patterns will be simultaneously measured. Heart rate will be recorded using a 3-lead electrocardiogram attached to a light-weight (<300 g) wearable ME6000 data acquisition computer (Mega Elektronika, Inc). Respiration will be measured using a nasal thermistor attached to an infrared end-tidal volume gas monitor (Capnomac Ultima, Ohmeda Inc.). Beat-to-beat blood pressure will be measured from a cuff placed on the finger using a Portapress-2 device (FMS, Inc), and galvanic skin conductance will be measured using an AD Instrument MLT116F (AD Instrument, Colorado Springs, CO).  The effects of perturbation to the cardiovascular system will be evaluated from the well-validated sit-to-stand test.^155^ Standing following prolonged sitting (≥5 min) results in an immediate elevation in HR, with relative greater change in HR response reflective of impaired cardiovascular regulation. The maximum change in HR (ΔHR) evoked from the sit-to-stand test will be quantified. ΔHR will be calculated by subtracting the minimum HR during sitting from the maximum HR during the subsequent bout of 1 min standing.  *Balance measures:* Steady-state standing balance dynamics will be assessed during eyes-open quiet standing as well as sitting. With arms at the side and bare feet shoulder width apart, subjects will be asked to stand as still as possible and to visually fixate on an “X” drawn on a wall approximately 3m away at eye-level. Center of pressure (COP) displacement will be recorded with a standard force plate (Kistler Instruments Corp, Amherst, NY). To collect sufficient COP data for complexity analysis, 1 min of continuous standing will be completed. This protocol will repeat for the sitting component of the test, with modifications made for the now seated subject.  The effects of visual and cognitive perturbations will also be evaluated. For the visual perturbation, subjects will stand similar to above, except with eyes-closed.^58^ For the cognitive perturbation, subjects will perform the dual task of counting backwards, out loud, in multiples of three, while attempting to repeat the steady-state protocol. Subjects will wear an MP3 recording device attached to their person or nearby to record verbal dual task cognitive test performance. This cognitive dual-task is commonly used to challenge standing balance in both healthy and movement disordered populations.^72^ To avoid potential effects of learning, subjects will begin each trial from 500, 499, or 498, in random order.  To account for potential trial-to-trial variability, three 1 min trials will be completed for each condition (steady-state, eyes-closed, dual task). Trials will be randomized and at least one minute rest will be given between each trial. During the first trial, the subject’s feet will be outlined with chalk to ensure consistent foot placement. A trained spotter will provide stabilizing assistance if necessary.  As one's balance is influenced by breathing, the effects of breathing frequency on standing balance will also be examined during one 4 min trial of standing on the force plate. Following 30sec of normal breathing, subjects will be asked to breath in rhythm to a metronome for three minutes. Metronome frequency will change every 30sec to obtain the following breathing frequencies: 50, 40, 30, 20, 10 and 5 breaths/min. A final 30sec of normal breathing will be completed to finish the test. The subject will be given time to practice breathing in rhythm to the metronome prior to the test. They will be reminded to return to their normal breathing patterns should they feel uncomfortable or light-headed during the test, and encouraged to sit or rest at any time. A trained spotter will remain behind the subject at all times.  *Gait measures:* Steady-state gait dynamics will be assessed during over ground walking at preferred speed. Subjects will walk along a long corridor (~75m) that is wide enough (~5m) to enable smooth turning. To record consecutive stride-to-stride durations, subjects will have foot-switches (Mega Elektronika, Inc) inserted into the shoes and the ME6000 data acquisition monitor attached to the waist. To collect the sufficient number of steps required for complexity measures, 20 min of continuous walking will be completed.The effects of a locomotor perturbation on gait speed, an indicator of gait health and overall function,^156^ will be assessed during continuous over ground walking while performing the same cognitive dual task as in balance testing. Subjects will complete three 1 min trials while counting backwards, out loud, in multiples of three.^157^ Dual tasking decreases walking speed.^72^ The distance walked during each trial will be recorded and used to calculate average speed. *Assessment of function and health-related quality of life*  Multiple clinical tests of physical and mental function will further characterize the sample, evaluate correlations between complexity measures and function, and assess the impact of Tai Chi and age on these outcomes.  *Maximum Walking Speed*: Performance in this common, easily administered clinical test is associated with functional decline.^158^ Subjects will walk in a straight line as fast as possible, without running, on a pre-measured 11m course. The time taken to walk 5m, from the 3m to 8m mark will be recorded and used to calculate maximal walking speed (m/s).  *One-legged standing balance*: This test will be assessed according to Vereeck et al.^159^ Timing will start when the subject has assumed the proper position on their preferred leg and verbally indicates readiness to begin the test. Timing will stop when the subject disengages from the starting position (i.e., the suspended foot touches the floor or the hands touch support surface) or when the 30 sec time limit is reached. The test will be conducted in the corner of a room, and the subject will be instructed to reach for the wall should they feel unstable. Three trials will be completed for eyes-open and eyes-closed conditions, and the greatest duration (sec) for each condition will be used for analysis. This test has been correlated with fall risk in older adults.^160^  *Lower-Extremity Muscular Power*: Maximal power output of the lower extremities will be estimated by assessing maximum vertical jump height (m) according to Bosco.^161^ In a study of more than 6000 women and men aged 40 to 85 years, Fujita et al^162^ determined this test to be safe for community-dwelling older adults, and that those with relatively low vertical jump scores had higher mortality rate over the six year follow-up period. Furthermore, as compared to lower-extremity muscular strength, power appears to be closely related to fall-risk^163^ and physical function.^164^ Subjects will complete a standard warm-up consisting of five sub-maximal jumps. Subjects will then complete three countermovement jumps on a stationary Kistler force plate (Kistler Instruments Corp, Amherst, NY). The “flight-time” for each jump, determined from the force plate reading, will be used to determine the maximum height reached by the subject’s center of mass using the Bosco method.^161^  *Range of Motion*: Bilateral hip, knee, and ankle joint passive range of motion (degrees) will be measured by a trained investigator ([name]) using a goniometer and standard procedures^165^ Lower body flexibility will also be assessed using the validated Chair Sit and Reach test.^166^  *Electrical Potential:* Skin surface electrical potential will be measured at select segments along the arms and legs, using 8 surface band electrodes (EL-506, Biopac, Goleta, CA) – 2 electrodes per extremity.  The electrodes will be connected to a data acquisition unit (Powerlab ML-880, AD Instruments, Colorado Springs, CO). This procedure tests the hypotheses exploring relationships between electrical potential and dynamics of other physiological measures (e.g. blood pressure and breathing).  *Physical Activity Levels:* In addition to Tai Chi training, general daily physical activity levels may influence both physical and cognitive function. The amount and intensity will therefore be recorded using the Physical Activity Status Scale (PASS).^167^ The PASS scale is an extension of the four-category scale used by Jones and associates^168^ to quantify leisure exercise levels. Each subject will be asked to estimate his or her general physical activity during the previous week using an 11-point scale (i.e., 0-10). The scale quantifies physical activity duration by a combination of the minutes of exercise per week and the intensity of this exercise (heavy, modest, or none). The concurrent validity of the scale has been documented in both men and women and scores correlate with maximal oxygen consumption in younger and older adults.^169,170^  *Grip strength:* Maximum grip strength is widely considered a simple and reliable measure that is correlated with mortality/survival, and disability, and overall function in middle-aged and older adults.^171^ Grip strength will be measured using a handgrip dynanometer Grip D (Takei Scientific Instruments, Tokyo, Japan). Subjects will be asked to grip the instrument with their dominant hand with maximum force. Measurements will be recorded to the nearest 0.5 kg, repeated three times and averaged. *Timed Up and Go Test:* This is a validated test for quantifying functional mobility that may also be useful in following clinical change over time. Patients begin in a seated position, stand up from a chair, walk a short distance (3 meters, ~10 feet) at a comfortable pace, turn around, return, and sit down again. This test will be timed by the blinded research assistant. The patient will repeat the test and the times will be averaged. The test is quick, requires no special equipment or training, and is easily included as part of the routine medical examination. *Functional Reach:* This standardized test is a measure of balance and is the difference, in inches, between arm's length and maximal forward reach, using a fixed base of support (such as a wall). This test can be used to detect balance impairment, change in balance performance over time, and in the design of modified environments for impaired older persons. The test utilizes a 48-inch measuring device or "yardstick".A reach of less than or equal to a certain level could be predictive of fall risk.  *SF36*: This health-related QOL instrument consists of 36 multiple choice items scored on a 0 to 100 scale of improving health status for each of 8 domains: physical functioning, role limitation due to physical problems, bodily pain, general health, vitality, social functioning, role limitations due to personal or emotional problems, and mental health. The SF-36 has been validated in a variety of populations including young and old healthy individuals, and patients with chronic medical problems, and has good test-retest reliability.^172,173^  *Cognitive function*: Cognitive function will be assessed with validated measures of executive function, working and short-term memory. The Trail Making Test (TMT) is a widely used instrument that is administered in two parts.^174^ TMTa is a visual-scanning task; the time required to draw lines sequentially connecting numbered circles from 1 to 25 is recorded. TMTb assesses time required to connect the same number of circles in an alternating sequence of numbers and letters. TMTb is considered to evaluate executive control, and is correlated with other executive function measures.^175^ TMT is a sensitive indicator of overall neurological impairment,^174^ and has good reliability.^176^ The Controlled Oral Word Association Test (COWAT) examines working memory span.^177^ COWAT requires the participant to produce as many words as possible that begin with a given letter of the alphabet (F,A,S). There is 1 minute allowed for each of the three letters. The score is the sum of all acceptable words produced in the three trials. COWAT has good reliability and validity.^177-179^ The Backwards Digit Span Test (BDS) is a widely used measure of short-term memory, i.e. the number of digits a person can absorb and recall in correct serial order. Two trials of eight number sequences are read aloud. The number sequences start out easy, with just two numbers, and get progressively more difficult, the last being nine digits. Scores are based on the number of sequences correctly recalled (i.e., until the participant consecutively fails two trials of the same digit span length). BDS has good reliability and validity.^177^ All three measures have been employed in studies evaluating the impact of exercise on cognitive function in elders.^1,2^  *Mini-Mental State Examination (MMSE)*: This is a short assessment instrument used to grade cognitive function (orientation to time and place, registration, memory, attention and concentration, praxis, constructional and language capacity, ability to follow commands).^180^ It is used widely in primary care and in community based research settings.^181,182^ The inter-rater reliability of the MMSE is 0.83.^180^ MMSE will be used only as a screening tool; only participants with scores ≥24 will be included.  *Profile of Mood States (POMS):* This is a well-validated instrument for assessing emotional states that are transient and expected to respond to clinical intervention.^185^ It has been widely used to assess the effects of exercise interventions. The instrument consists of 65 single-word items rated on a 5-point scale to indicate recent mood in 6 dimensions: tension/anxiety, depression/dejection, anger/hostility, vigor/activity, fatigue/ inertia, and confusion/bewilderment. A decreased total score denotes an improved emotional state. Test-reliability coefficients are reported to range from 0.65 to 0.74.^185^ Studies of Tai Chi have reported improvement in mood, decrease in anxiety, and enhancement in vigor as measured by the POMS scale.^186^  *Expectancy and Satisfaction*: We will assess the degree to which participants believe that Tai Chi will be beneficial to their health using an instrument used in a number of prior CAM studies. Participants in both groups at baseline will be asked: ‘How confident are you that Tai Chi will improve your health?’; ‘How confident are you in recommending Tai Chi to a friend for health promotion?’; ‘Does doing Tai Chi for health make sense to you?’. Response choices range from 1 through 5, with 1 representing ‘not at all’ confident and 5 ‘extremely’ confident. For participants in the Tai Chi group, satisfaction with the intervention will be assessed by asking them to score the following four statements (5 point scale; 1 strongly agree, 5 strongly disagree) at 3 and 6 month visits: ‘Overall, I am satisfied with my Tai Chi experience in the study’; ‘Overall, I am satisfied with my Tai Chi school’; ‘Overall, I am satisfied with the tai chi teachers I am training with’; ‘I would recommend the Tai Chi program I am enrolled in to a friend or relative.’  *Qualitative Exit Interview:* At the end of your 6 month visit, subjects assigned to the Tai Chi group will also be asked to complete a qualitative exit questionnaire comprised of 6 questions. We will audio tape the answers to these questions. The audio file will be erased once it has been transcribed, within a year of the interview date. Subjects may decline any question they do not wish to answer, and they may decline from having their answers audio taped.  **Survey regarding control groups for future studies**  At the end of our initial phone screen, all participants will be asked a series of questions to explore the types of activities they would consider worthy of participating in, and willing to be randomized to, in a future hypothetical trial related to healthy aging. A list of specific activities (e.g., exercise classes at local YMCA’s, academic lecture series on healthy aging, and group walking classes) will be presented, and for each activity, participants will be asked to respond with one of the following assessments: very interested in participating, moderately interested in participating; not at all interested in participating. Results from this survey will help determine the controls we might employ in a follow-up multi-arm study.  **Data processing**  Analog signals from the ECG and balance platform will be recorded at 1000 Hz using Labview NIDAQ software (National Instruments Data Acquisition System 64 Channel/100 Ks/s, Labview 6i, Austin, TX). Foot switch signals will also be recorded at 1000 Hz using the ME6000 and accompanying software.  For cardiovascular measures, beat-to-beat HR will be determined from the R-wave on the ECG. All data will be visually inspected for accuracy of R-wave detection, artifacts and occasional extra-systoles using software written in our laboratory. Ectopy and artifacts will be removed using a linear interpolation algorithm. The HR interval time-series will be used to compute steady-state complexity measures. For comparison with complexity measures, HR data will also be analyzed using spectral analysis methods we have developed and employed in our prior studies.^137,144^  For balance measures, the acquired anterioposterior (AP) and mediolateral (ML) (COP) time series will be digitally filtered with a zero-lag fourth-order Butterworth low-pass filter with a 5 Hz cutoff frequency. AP and ML COP time-series will be used to compute steady state complexity measures (see D.6). For comparison with complexity measures, the traditional measures of average displacement (mm) in the AP and ML directions will also be determined by computing the mean scalar displacement along each axis.^189^ To assess the effects of visual and cognitive perturbation, average ML and AP displacement will also be calculated for the eyes-closed and dual task conditions. As each perturbation increases the magnitude of COP displacement, the effect of perturbation will be defined by the percent change in average ML and AP COP displacement during the perturbation condition as compared to the steady-state condition.  For gait measures, on/off foot switch data will be used to determine consecutive stride durations (time from initial contact of one foot to the subsequent contact of the same foot) during the 20 min walk. The resulting stride duration time series will be used to compute steady-state complexity measures. To assess the effects of the dual task perturbation (known to decrease walking speed), the percent change in walking speed during dual task as compared to the steady state condition will be computed.  **Computation of complexity measures**  Our team has extensive experience quantitatively analyzing complex physiologic signals – particularly for signals to be obtained in this study. Two principal complexity metrics––Detrended Fluctuation Analysis (DFA) and Multiscale Entropy (MSE)––were developed by team members.^6,26,51^ DFA quantifies long-range correlation properties (fractality) of a signal. Unlike alternative approaches (e.g., Fourier spectral analysis and Hurst analysis), DFA permits the detection of intrinsic self-similarity embedded in a seemingly nonstationary time series. DFA has been successfully applied to a wide range of simulated and physiologic time series in recent years.^5,13,18^ Multiscale Entropy quantifies the information content of a signal over multiple scales. Compared to other entropy-based methods, MSE uniquely accounts for dynamical information encoded in physiologic signals over multiple scales and therefore is able to distinguish between highly irregular random (uncorrelated) signals and truly complex ones.^52,190,191^ Extensive information on these measures, including details of algorithms, tutorials, and examples of their application is provided at Research Resource for Complex Physiologic Signals ([www.physionet.org](http://www.physionet.org)). This website is sponsored by NIH, and was developed by members of our team. |

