### Statistical Considerations

| ***Sample Size Justification:*** Our analysis will be based on a longitudinal regression analysis in which we do not have an estimate of the within-participant correlations. In the worst case, the two follow-up measures provide no more information than a single follow-up, and the power calculation is equivalent to that for a simple t-test. With 30 participants in each group, we would have 50% power to detect an effect size of 0.52 (i.e., the sample size provides 50% sensitivity to detect a difference between groups .52 times the standard deviation of the outcome measure) and 80% power to detect an effect size of 0.74 for each of the main effects. Our primary hypothesis, however, is an interaction effect. Our sample size provides at least 50% power to detect an interaction effect size of 1.03, under this worst-case scenario. At the other extreme, if the two follow-up observations are independent, we will have 50% power to detect an interaction effect size of 0.72 and 80% power to detect an effect size of 1.03. The use of regression models further increases power by accounting for additional sources of variability. In our heart failure study, the mean difference in MSE change between Tai Chi and control was 2.26, which translates to an effect size of 1.2. Preliminary COP data from our Tai Chi for osteopenia study showed a similar effect. Therefore, we think changes of this magnitude will likely be present in the proposed study and our study has adequate power.  For Study Aim 3, we will in essence be comparing the 30 tai chi experts to the 60 novices. After adjusting for the effect of age, we will have 80% power to detect a difference between naïve and tai chi experts of approximately 0.65 times the residual error.  For Study Aim 4, we will be comparing the baseline COP and balance measures in the various age categories (15 participants age 25-35, and 20 participants in each of the older groups). This sample will provide at least 82% power to detect a difference between the young group and the average of the older groups equal to the within-group standard deviation.  ***b. Data Analysis***  *Aim 1*: We are interested in comparing the change over time in the Tai Chi students versus the controls. The primary analysis will use an intention-to-treat paradigm, i.e., participants will be evaluated on the basis of group assigned by randomization without regard to subsequent adherence. Since this is a pilot study, we will not impute values for missing data; however, the statistical models we are using will include all available data. We recognize that some participants may drop out before the follow-up evaluation and that some outcome measures may not be evaluable for some participants. We will make no adjustment for multiple testing. A secondary ‘per-protocol’ analysis will be limited to participants who were compliant (attended 70% of classes and completed at least 70% of home sessions).  Our primary analysis will employ linear mixed effects regression models that examine change over time (i.e., slope) for each outcome measure (i.e., the complexity measures, MSE and detrended fluctuation analysis) for each of the systems (i.e., heart rate, balance and gait). The models will incorporate a random intercept and a random slope for each participant. The models will be of the form:  ****  for individual  in treatment group  where the random intercept , the random slope , and the residual error . The focus of the primary analyses is on , which evaluates whether treatment is associated with the slope over time.  We will also conduct sensitivity analyses that incorporate additional covariates into the models, including age, gender, baseline physical and mental health, BMI, expectancy, and exercise behavior. We are particularly interested in examining age with a focus on assessing whether age substantially reduces the variability of the random effects, i.e., whether it explains a substantial proportion of between-person variability in baseline complexity and slope.  Analyses of secondary outcomes will follow the same general analytic approach. We will use mixed effects models to examine the effects of Tai Chi training over time on physical and cognitive function (exercise capacity, balance, upper and lower extremity strength, cognitive function, and quality of life) and adaptive capacity (change in heart rate, change in COP displacement, change in stride variability).  *Aim 2*: We hypothesize that function and adaptive capacity are associated with complexity. We will first examine the association between complexity measures and function/adaptive capacity at baseline. We will calculate Pearson correlation coefficients between the complexity measures (MSE and detrended fluctuation analysis) and the measures of function/adaptive capacity. To examine the independent association between complexity and function/adaptive capacity, we will fit ordinary least squares regression models using the function/adaptive capacity measures as the dependent variable. Independent variables will include age and sex as well as any other baseline characteristics associated with the function variable. We will add the complexity measure to this model and evaluate the Wald test and the change in R^2^.  We will also investigate whether changes in complexity are associated with changes in function/adaptive capacity. We will fit linear regression models with change in function/adaptive capacity as the dependent variable and change in complexity as the independent variable of interest. Since we will have 2 observations per participant (change at 3 months and change at 6 months), we will use generalized estimating equations methods (GEE) to account for the within-person correlation. Independent variables will include the measure of function/adaptive capacity at baseline, age, sex, treatment group and time (3 vs. 6 month).  Further, we hypothesize that complexity is the primary mediator of the association between Tai Chi and improvements in adaptive capacity. We will examine this using the approach recommended by Judd and Kenny.^193^ For example, to examine whether multi-scale entropy of balance mediates the effect of Tai Chi on center of pressure response to a dual cognitive task among the older participants, we will fit 3 regression models: regress MSE on Tai Chi use; regress COP response on Tai Chi; and regress COP response on MSE and Tai Chi use. The associations seen in these models determine the existence and strength of mediation.  Despite the implicit directionality of our hypotheses, all tests will be two-sided. We recognize that we are examining a moderate number of outcomes in this study. Since it is a pilot study and has limited power, we do not intend to adjust for multiple testing.  *Aim 3:* Our goal is to compare the complexity measures, function, and resilience to perturbations between tai chi experts and those with no tai chi training or only limited training. We expect responsiveness to decrease as a function of age among the tai chi naïve participants (i.e., both randomized groups combined). We hypothesize that tai chi experts will have a generally higher level of responsiveness, and that their responsiveness will decline with age at a slower rate than naïve or novice practitioners. To examine these questions, we will fit linear regression models to the baseline responsiveness measures for all participants:    where TC is an indicator variable for the tai chi experts.  is an estimate of the difference in responsiveness between tai chi experts at age 50,  is an estimate of the change in responsiveness per year for the novice group, and is the difference in rate of change between novices and tai chi experts.  We will fit a similar model to compare the tai chi experts to the naïve and novice groups using the 6-month data for the randomized patients and the baseline data for the tai chi experts. The group variable will be a categorical variable with 3 levels.  *Aim 4:* We will calculate sample means for each of the outcomes in each age group. We will use standard one-way analysis of variance to compare the four groups. If the overall test is significant, we will use Dunnett’s test to compare the young group to each of the older age groups. |

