### C. Subject Selection

| **Study population and recruitment procedures**  Identification of Arms 1 and 2 (Tai Chi naïve older adults)  A total of 60 healthy older adults (50-79 years old) will be recruited for our study. Recruitment will target community dwellers living within the Greater Boston area. Identification of potential study participants will include a variety of procedures that we have successfully employed in our prior studies. These include: 1) Posting study brochures and flyers in ambulatory clinics associated with BIDMC’s Department of General Medicine and Primary Care and Department of Gerontology (approximately 4,000 and 1,000 patients, respectively); 2) Direct referrals from providers in these and other clinics with whom we have a long-standing working relationship (e.g. [name] is the Chair of Gerontology and Drs. [name] and [name] are staff physicians in General Medicine); 3) Advertising in various publications including the Harvard Cooperative Program on Aging newsletter on healthy aging (disseminated 3 times a year to more than 9,500 older adults) and other local periodicals targeting older adults (e.g. *Fifty Plus Advocate, The Senior Times*), as well as on internet based resources such as Craig’s list; 4) BIDMC Syncope and Falls in the Elderly (SAFE) laboratory IRB approved database, whereby [name] provides names of potentially eligible participants who have offered to participate in SAFE lab studies; 5) Flyer placement in the communities surrounding the study’s network of Tai Chi schools (e.g., community bulletin boards, libraries).  Identification of Arm 3 (Tai Chi Expert Group)  A total of 30 healthy older adults (50-79 years old) each with over five years of tai chi practice will be recruited for our study. Recruitment will target tai chi experts living within the Greater Boston area. Potential study participants will be identified through advertisement and presentations given by PI and/or other co-investigator at Tai Chi schools.  Identification of Arm 4 (Young Comparison Group)  A total of 15 healthy young adults (25-35 years old) with no prior tai chi experience will be recruited for our study. Recruitment will target young adults living within the Greater Boston area. Potential study participants will be identified through advertisement and presentations given by PI and/or other co-investigator in the community.  5.2.2. Eligibility criteria  Arms 1 and 2: Recruitment will focus on healthy, relatively sedentary, older Tai Chi-naïve adults. Eligibility criteria will be based on screens conducted by study staff and confirmed by BIDMC GCRC nursing staff.  Arm 3 (Tai Chi Expert Group): Recruitment will focus on healthy tai chi experts with over five years of tai chi practice. Eligibility criteria will be based on screens conducted by study staff and confirmed by BIDMC GCRC nursing staff.  Arm 4 (Young Comparison Group): Recruitment will focus on healthy, relatively sedentary, young Tai Chi-naïve adults. Eligibility criteria will be based on screens conducted by study staff and confirmed by BIDMC GCRC nursing staff.  Arms 1 and 2 Inclusion criteria:  • Ages 50-79  • Living within the Greater Boston area  • Willing to adhere to 6 month Tai Chi training protocol  • Patients with a history of both solid and hematologic cancer (≥ 5 years of complete remission and who do not require chronic maintenance chemotherapy). Chronic use of hormonal agents such as aromatase inhibitors and GnRH analogs, however, are permissible with the understanding that these agents do not substantially alter the cardiovascular, autonomic, and postural control systems.  • Patients with prostate cancer (Stage I or II only)  • Patients with dermatological cancer that has been completely resected with no additional incidence.  Arm 3 (Tai Chi Expert Group) Inclusion criteria:  • Ages 50-79  • Have over five years of Tai Chi practice  • Patients with history of both solid and hematologic cancer (≥5 years of complete remission and who do not require chronic maintenance chemotherapy). Chronic use of hormonal agents such as aromatase inhibitors and GnRH analogs, however, are permissible with the understanding that these agents do not substantially alter the cardiovascular, autonomic, and postural control systems.  • Patients with prostate cancer (Stage I-II)  • Patients with dermatological cancer that has been completely resected with no additional incidence.  Arm 4 (Young Comparison Group) Inclusion criteria:  • Ages 25-35  • Living within the Greater Boston area  • Patients with a history of both solid and hematologic cancer (≥ 5 years of complete remission and who do not require chronic maintenance chemotherapy). Chronic use of hormonal agents such as aromatase inhibitors and GnRH analogs, however, are permissible with the understanding that these agents do not substantially alter the cardiovascular, autonomic, and postural control systems.  • Patients with prostate cancer (Stage I or II only)  • Patients with dermatological cancer that has been completely resected with no additional incidence.  Exclusion Criteria:  • Chronic medical conditions, including: cardiovascular disease (myocardial infarction, angina, atrial fibrillation, or presence of a pacemaker), stroke, respiratory disease requiring daily use of an inhaler, diabetes mellitus, malignancies (patients with diagnosis of active cancer < 5 years ago requiring ongoing chemotherapy or use of cytotoxic agents), neurological conditions (e.g., seizure disorder, Parkinson’s, peripheral neuropathy), or other neuromuscular or musculoskeletal (requiring chronic use of pain medication) disease  • Acute medical condition requiring hospitalization within the past 6 months  • Self-reported (current) smoking or alcohol/drug abuse  • Uncontrolled Hypertension (resting SBP > 160 or DBP > 100mm Hg)  • Abnormal heart rate (resting HR > 100 bpm; <50bpm)  • Abnormal ECG (supraventricular tachyarrhythmia, atrial fibrillation, significant ST wave abnormality, 2^nd^ and 3^rd^ degree heart block)  • Pregnancy  • Current use of prescription medications including cardio- or vaso-active drugs and medications that can affect autonomic function including Beta agonists and antagonists, drugs with anticholineric properties (e.g. tricyclic antidepressants or anti psychotics), and cholinesterase inhibitor^[[1]](#footnote-1)^  • Self-reported inability to walk continuously for 15 minutes unassisted^[[2]](#footnote-2)^  • Regular Tai Chi practice within past 5 years‡‡  • Regular participation in physical exercise on average 4 or more times per week‡‡  Arms 1 and 2 Recruitment, enrollment and randomization procedures  Potential participants who learn about our prospective study from brochures, referrals, or advertisements will be directed to call the study coordinator, who will conduct an initial eligibility screen by telephone, and schedule potentially eligible individuals for a visit at the BIDMC Clinic Research Center (CRC) for further screening. The coordinator will also discuss the randomization process and emphasize the 6 month commitment for those randomized to Tai Chi. Phone screen eligible individuals will be asked to visit at least one Tai Chi school prior to the on-site CRC screening visit. At the end of our initial phone screen, all participants will be informed about the Syncope and Falls in the Elderly (SAFE) Laboratory Research Recruitment Repository Database, and if they agree, their contact information will be given to [name]. [name] is the director of the SAFE Lab, PI of the Research Recruitment Repository Database, and a co-investigator on this study. Prior to baseline testing, individuals will undergo formal consenting following BIDMC and NIH guidelines. Following baseline testing, participants will be randomly assigned to one of two interventions, Tai Chi or wait list control.  Our study statistician, [name] will be responsible for randomization procedures. We will stratify participants by age (50-59, 60-69, 70-79), generate treatment assignments using a permuted-blocks randomization scheme with randomly-varying block sizes, and seal the treatment assignments in opaque, sequentially numbered envelopes for each stratum. The use of stratification will limit the potential for confounding by age. Upon randomization, study staff will enter the participant’s name and medical record number into a randomization log. All randomization materials will be stored in a locked file, with access limited to non-blinded study personnel.  Arm 3 (Tai Chi Expert Group) Recruitment and enrollment procedures  Potential participants who learn about our prospective study from referrals or advertisements will be directed to call the study coordinator, who will conduct an initial eligibility screen by telephone, and schedule potentially eligible individuals for a visit at the BIDMC Clinic Research Center (CRC) for further screening.  Arm 4 (Young Comparison Group) Recruitment and enrollment procedures  Potential participants who learn about our prospective study will be directed to call the study coordinator, who will conduct an initial eligibility screen by telephone, and schedule potentially eligible individuals for a visit at the BIDMC Clinic Research Center (CRC) for further screening.  Remuneration  Arms 1 and 2: All parking expenses associated with CRC visits will be paid for by the study. Eligible and consented participants who complete outcome assessments will be paid $100 at study midpoint (3 months), and $100 at study endpoint (6 months) with a maximum compensation of $200. Participants who complete the screening process but are not eligible to participate further will receive $50.Tuition for all Tai Chi training over the 6-month study period will be paid for by the study. Participants in the control group will also be offered 3 months of free Tai Chi training at the completion of the study at their choice of school within our network.    Arm 3 (Tai Chi Expert Group) Remuneration:  All parking expenses associated with CRC visits will be paid for by the study. Eligible and consented participants who complete outcome assessments will be paid $200 following single visit.  Arm 4 (Young Comparison Group) Remuneration:  All parking expenses associated with CRC visits will be paid for by the study. Eligible and consented participants who complete outcome assessments will be paid $50 following single visit. |

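### The secondary per-protocol rule can be met only in the Tai Chi arm, so in practice it sets self-selected adherers against all controls, a contrast that randomisation does not protect and that may be biased, probably towards Tai Chi.

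*Protocol*

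**What the plan says.** All of this is in the Protocol.

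- **Per-protocol rule** (Statistical Considerations, Data Analysis, Aim 1): "A secondary ‘per-protocol’ analysis will be limited to participants who were compliant (attended 70% of classes and completed at least 70% of home sessions". Nothing says how the rule applies to each arm.
- **Contrast of interest** (same section): "We are interested in comparing the change over time in the Tai Chi students versus the controls".
- **Primary analysis** (same section): intention-to-treat, in which "participants will be evaluated on the basis of group assigned by randomization without regard to subsequent adherence".
- **Training prescribed** (Study Design): "Participants randomized to Tai Chi will be required to attend, on average, two classes per week over the six months of the intervention". The next sentence, about the same people, adds: "They will also be asked to practice a minimum of 30 minutes, two additional days per week".
- **Control condition** (Study Design): participants are "randomized to either six months of Tai Chi training, or to a waitlist control receiving standard medical care".
- **Training for controls** (C. Subject Selection): "Participants in the control group will also be offered 3 months of free Tai Chi training at the completion of the study", which is after the 6-month measurement.

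**The concern.** A per-protocol set should say what following the protocol means in each arm. Here compliance is defined only by classes and home sessions, and controls have neither. The analyst must therefore add a rule that the protocol does not give. The obvious one is to drop Tai Chi participants who fall below 70% and keep every control.

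That leaves in the control arm the people who would not have adhered had they been assigned to Tai Chi, while their counterparts in the Tai Chi arm are removed. If the tendency to adhere is related to how a participant would have changed without training, the two groups differ in slope even when Tai Chi does nothing. The model tests slopes, so a difference in baseline level alone would not cause this; the relation has to be with change.

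The pilot is meant to inform a definitive trial on compliance, on how effects vary with dose and on effect size. The per-protocol comparison is the only adherence-based treatment comparison stated. A reader looking for the effect among those who trained would turn to it.

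**Working it through.** **1. Who can meet the rule.** Taking six months as 26 weeks (my assumption), two classes a week is 26 × 2 = 52 classes, and home practice on two further days is 52 sessions. Seventy per cent is 0.70 × 52 = 36.4, so 37 of each. Controls are prescribed none of either before their last measurement, so 0 of 30 can qualify. Read literally, the between-arm contrast cannot be estimated.

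**2. The plan's own figures, for scale.** The per-protocol analysis has no stated figure. The protocol does give power for 30 per group in its simple t-test case: 80% at effect size 0.74 and 50% at 0.52. A two-sided t-test at 5% (the level is assumed; the protocol says only two-sided) returns 80.5% and 50.8%. The stated figures reproduce.

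**3. Bias in the workable reading.** Assumptions: change scores with SD 1, no true effect, 30 randomised per arm, all controls kept, no covariate adjustment. A share p of the Tai Chi arm complies. Adherence tendency is normal and has correlation r with the untreated change. With c the standard normal cut-off exceeded with probability p, and φ the normal density:

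- λ = φ(c)/p
- bias = r·λ
- variance among compliers v = 1 − r²·λ(λ − c)
- SE = √[v/(30p) + 1/30]
- error rate = P(|Z + bias/SE| > 1.96)

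Worked case, p = 0.65 and r = 0.3: λ = 0.570, so bias = 0.3 × 0.570 = 0.171. Then v = 1 − 0.09 × 0.544 = 0.951, SE = √(0.951/19.5 + 1/30) = 0.2865, and bias/SE = 0.597. The error rate is 9.2%.

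| Compliant | λ | r = 0.2 | r = 0.3 | r = 0.4 |
|---|---|---|---|---|
| 50% | 0.798 | 0.16 SD, 8% | 0.24 SD, 12% | 0.32 SD, 18% |
| 65% | 0.570 | 0.11 SD, 7% | 0.17 SD, 9% | 0.23 SD, 13% |
| 80% | 0.350 | 0.07 SD, 6% | 0.11 SD, 7% | 0.14 SD, 8% |

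**4. Check by simulation, and other inputs.** With 20,000 simulated trials per setting and a t-test, 70% compliance and r = 0.3 give a bias of 0.15 SD and an error rate of 8.2%. At r = 0 there is no bias and the error rate stays near 5%. At r = −0.2 and 70% compliance the bias is −0.10 SD. At 90% compliance and r up to 0.5 the bias is at most 0.10 SD and the error rate at most 6.3%.

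**5. What the alternative estimate does.** With control dose set to zero, the instrumental-variable estimate per unit of training is the intention-to-treat effect divided by mean Tai Chi dose. Suppose, for illustration, that mean dose is 65% of that prescribed. The effect at full prescribed dose is then the intention-to-treat effect ÷ 0.65, or 1.54 times it. Under the same unit-SD simplification the intention-to-treat SE is √(1/30 + 1/30) = 0.258. The rescaled SE is 0.258 ÷ 0.65 = 0.397, ignoring uncertainty in mean dose. The estimate and its SE scale together, so with no effect the test is essentially the intention-to-treat test and keeps its error rate.

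**The case against.** **The rule obviously concerns the Tai Chi arm.** Aim 1 is framed as Tai Chi against controls, and only one arm has classes. A reader might infer that the analysis will have no comparator. That presses the wording too far: any analyst would keep the controls. What stands is that the protocol fixed this rule rather than deferring it, and that the natural repair leads to one-sided exclusion.

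**This is the ordinary weakness of a per-protocol analysis, and the plan ranks it accordingly.** It is secondary, in a pilot, behind an intention-to-treat primary analysis. This stands and limits the weight of the point. It does not make the comparison a randomised one.

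**The direction of bias is assumed.** A reader might infer that the result will favour Tai Chi. The protocol has no figure to support that, and step 4 shows the bias vanishing or reversing. Only a probable direction can be claimed.

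**Covariate models are planned.** The sensitivity analyses add age, gender, baseline physical and mental health, BMI, expectancy and exercise behaviour. These could absorb part of the selection, and the bias figures above are unadjusted. However, the protocol does not tie those models to the per-protocol set.

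**Nothing says the per-protocol estimate will size the next trial.** Correct. The risk is one of use, not a stated plan.

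**Sessions against hours.** Table 1 lists "Hours of home practice/month" while the rule counts sessions, so a reader might infer that the criterion cannot be computed. The documents do not show this: the home practice logs are the source and may well record sessions.

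**Conclusion.** The point holds in a limited form. The per-protocol rule, as fixed, can be met only by the Tai Chi arm, and its workable reading selects after randomisation in that arm alone. This may bias the slope contrast, probably towards Tai Chi. Under the assumed 50-80% compliance and correlation of 0.2-0.4, the bias with no true effect is 0.07-0.32 SD and the two-sided error rate is 6-18%, against a nominal 5%. Both inputs are assumptions. The bias disappears at zero correlation, changes sign below it, and is small when compliance is near 90%. The primary intention-to-treat analysis is untouched. The matter is worth correcting because the remedy is cheap and the protocol states no other adherence-based comparison.

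**What to change.** **Per-protocol set.** State that the 70% rule applies to the Tai Chi arm only and that all controls are kept. Label the comparison descriptive and non-randomised. Fit it with the baseline covariates that the Statistical Considerations section already lists for sensitivity analyses.

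**Effect of training received.** Report an instrumental-variable estimate as the adherence-adjusted result, with randomised arm as the instrument and training received (classes attended plus home practice, in one stated unit) as the dose.

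- Set control dose to zero and say that this is an assumption, since no procedure is described for recording Tai Chi practice in controls.
- Obtain the estimate by dividing the intention-to-treat mixed-model effect by the between-arm difference in mean dose. This uses all available data, whereas two-stage least squares on change scores would drop people without follow-up.
- State the limits: a wider interval, linearity in dose, no information on the shape of dose-response, and the assumption that assignment acts only through training, which is open to doubt with an unblinded waitlist.

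**Cost.** A few sentences in the analysis section and a few lines of code, using the attendance and practice records already planned. The price is lower precision: in the illustration above, an SE of 0.397 for the effect at full dose, against 0.258 for the intention-to-treat effect.
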